**Methods:**

This will be a parallel, two-arm, statistician-blinded, randomised evaluation. Clinically stable liver patients at 1 to 5 years post-transplant (*n* = 180) will be randomised in equal numbers to video clinic appointments (intervention) or standard face-to-face appointments (control). The intervention group will have outpatient appointments from home via a secure video link accessed through the UHB patient portal. All patients will complete baseline questionnaires before randomisation and electronic follow-up questionnaires after each follow-up appointment during the subsequent 12 months. The primary outcome is the difference in scores between groups for three domains of patient satisfaction, namely ‘convenience of location’, ‘getting through to the office by phone’ and ‘length of time waiting’ (modified Visit-Specific Satisfaction Instrument). Secondary outcomes include quality of life (EQ-5D-5 L), costs, clinical contacts and user experience. Statistical analysis will be descriptive and performed on an intention-to-treat basis. The primary outcome will be analysed using baseline and 3-, 6-, 9- and 12-month questionnaires (according to patient follow-up appointment frequency) and comparisons made between study arms. A within-trial cost consequences analysis will be undertaken on the economic data. Patients (*n* = 8), carers/family members (*n* = 6) and health professionals (*n* = 14) will be interviewed about the experience of video clinics and the interviews will be analysed using thematic analysis.

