### Outcome measures and data collection

Study outcomes and methods of data collection are summarised in Table 1.

**Table 1 Tab1:** Outcome measures, data collection instruments and format

Outcome measure	Data collection instrument	Format
Primary outcome		
(Change in) satisfaction in the VSQ-9 domains of ‘convenience of location’, ‘getting through to the office by phone’ and ‘length of time waiting’	Modified Visit-Specific Satisfaction instrument (VSQ-9) [26] within patient questionnaire	Baseline: paper At the following timepoints, after each appointment, in electronic or paper^a^ format: 3 months (if applicable) 6 months 9 months (if applicable) 12 months
Secondary outcomes		
Patient-reported health-related quality of life	EQ-5D-5 L [31] within patient questionnaire	Baseline: paper 6 months: electronic or paper 12 months: electronic or paper
Patient satisfaction scores in the other six VSQ-9 domains	VSQ-9 [26] within patient questionnaire	Baseline: paper At the following timepoints, after each appointment, in electronic or paper^a^ format: 3 months (if applicable) 6 months 9 months (if applicable) 12 months
Routinely collected clinical outcomes	Patient records	Routinely collected metrics
Number and length of clinical contacts, and instances of appointment non-attendance	Length of appointment, phone calls, myhealth@QEHB correspondence, crossover between study arms	Routinely collected metrics Clinician reporting Case report forms
Health service use	Patient questionnaire	Baseline: paper At the following timepoints, after each appointment, in electronic or paper^a^ format: 6 months 12 months
Costs (NHS perspective and societal perspective)	Patient questionnaire and routinely collected data	Baseline: paper At the following timepoints, after each appointment, in electronic or paper^a^ format: 3 months (if applicable), 6 months 9 months (if applicable) 12 months Routinely collected metrics
MyVideoClinic system performance	Failed appointments, service outages, telephone consultations	Routinely collected metrics
Clinical tests performed locally prior to video clinic appointment	Blood tests, blood pressure and weight	Case report form completed by clinician
Patient, carer and clinician experience	Semi-structured interviews	Semi-structured interviews

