#### Primary outcome measure

The combined satisfaction score for three domains of the modified VSQ-9 (convenience of location, getting through to the office by phone and length of time waiting) is the primary outcome for this study [26]. The VSQ-9 has been validated and used in previous studies conducted in different health settings [29], and an earlier version of this questionnaire (SVQ13) was used in a randomised controlled trial of virtual outreach in a UK context [30]. The VSQ-9 asks participants to rate their satisfaction with various aspects of their clinic appointment on a 5-point scale (poor, fair, good, very good, excellent). Scores are then transformed into a 0–100 linear scale, where higher scores denote higher levels of satisfaction. VSQ-9 data will be collected at baseline and after every video clinic or face-to-face appointment via patient questionnaires. A difference of 10 points between the intervention and control groups in the three selected domains of the VSQ-9 at study end (12 months) will be taken as clinically significant [30].

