### Statistical analysis

An interim analysis will be undertaken once 25% of the target recruitment sample have completed two appointments. This interim analysis will focus on crossover from the intervention to control groups due to patients being unable to complete their clinical testing locally. The findings from this interim analysis will be discussed with the study’s independent monitoring group as high rates of crossover have implications for the feasibility of the intervention and will reduce study power to detect significant differences between intervention and control arms in the outcomes of interest. The main data analysis will be undertaken on an intention-to-treat basis, although an unblinded per protocol analysis will also be performed for the primary outcome measure to assess whether similar results are obtained with regard to any statistically significant findings. It is acknowledged that younger patients may potentially find the intervention more beneficial due to greater familiarity with technology, so age will be controlled for and a sensitivity analysis will assess whether age has an independent effect on outcomes.

The characteristics of study participants at baseline will be summarised descriptively, with comparison of proportions tests used to assess any differences between intervention and control groups on the basis of sociodemographic and clinical characteristics. Analysis of the primary outcome measure (difference between groups in scores in three domains of the VSQ-9) will use independent *t* tests if data are normally distributed. If data are not normally distributed, the Mann–Whitney U test will be used. For patients with missing end-of-study VSQ-9 data, their most recently collected data will be used in the analysis. If participant numbers allow, subgroup analysis will assess patient satisfaction scores adjusting for the level of engagement that intervention patients had with myVideoClinic (i.e. those with 6 months or less of video clinic appointments vs. those with more than 6 months of video clinic appointments).

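### The named primary tests cannot adjust for age as promised, make no stated use of baseline VSQ-9, and under the Mann-Whitney branch do not target the 10-point mean difference

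*Protocol article*

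**What the plan says.** The Statistical analysis section describes the primary outcome as the "difference between groups in scores in three domains of the VSQ-9" and says that its analysis "will use independent *t* tests if data are normally distributed". The fallback follows: "If data are not normally distributed, the Mann–Whitney U test will be used". Earlier in the same section, after noting that younger patients may benefit more, the plan adds "so age will be controlled for and a sensitivity analysis will assess whether age has an independent effect on outcomes". It names no model for this.

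Other parts of the article describe the analysed quantity differently:
- Abstract, Methods: "The primary outcome will be analysed using baseline and 3-, 6-, 9- and 12-month questionnaires".
- Table 1: the primary outcome is "Change in) satisfaction in the VSQ-9 domains of" the three named domains, with the reference to change in brackets.
- Primary outcome measure: "A difference of 10 points between the intervention and control groups in the three selected domains of the VSQ-9 at study end", at 12 months, is the clinically significant effect. The same section says that "VSQ-9 data will be collected at baseline and after every video clinic or face-to-face appointment via patient questionnaires".

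Sample size and study power sizes the trial on that 10-point difference: 62 per group, raised to 90 per group for attrition.

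**The concern.** There are three linked problems.

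**Age.** A two-sample t test and a Mann-Whitney U test compare two groups and take no covariate. If age is to be controlled for in the primary comparison, neither test can do it. The sensitivity analysis does not settle the matter, because the sentence promises control for age and a sensitivity analysis as well.

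**Baseline and the analysed quantity.** Baseline VSQ-9 is collected from every patient before randomisation. A reader cannot tell whether the primary test uses the 12-month score or the change from baseline. The two have different precision, and neither is in general as efficient as adjusting for baseline.

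**The switch.** A normality check on the outcome data picks the test. The t test addresses a difference in mean points, and the Mann-Whitney test addresses the probability that a patient in one arm scores higher than a patient in the other. Each domain is rated on a 5-point scale and rescaled to 0–100, so the combined score is bounded and discrete and cannot be exactly normal. The fallback is a real prospect, while both the clinical criterion and the sample size are in mean points.

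**Working it through.** **Inputs from the article:** difference 10 points; power 80%; alpha 0.05 (taken as two-sided, since sidedness is not stated); 62 per group; 1:1 allocation; attrition 30%; 90 per group recruited. **Not in the article, so assumed:** the SD and the baseline-outcome correlation r.

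**1. The plan's own figure.** The usual formula is n per group = 2 × SD² × (1.960 + 0.842)² / 10². No SD is given, so 62 cannot be reproduced directly. Solved backwards:

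SD = 10 / [√(2/62) × 2.802] = 10 / (0.1796 × 2.802) = 19.87.

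With the t distribution it is 19.7. An SD of 20 gives 63 per group, so the plan's figure is consistent with an SD of about 20. For attrition, 62 / 0.70 = 88.6, rounded up to 89, close to the stated 90. Completers are 90 × 0.70 = 63 per group.

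**2. Power at 63 per group, SD 19.7** (noncentral t, two-sided 0.05).
- Raw 12-month score: effective SD 19.7, power 80.7%.
- ANCOVA on baseline: effective SD = 19.7 × √(1 − r²).
- Change score: effective SD = 19.7 × √(2(1 − r)), assuming equal SD at baseline and 12 months.

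| r (assumed) | ANCOVA SD | ANCOVA power | Change-score SD | Change-score power |
|---|---|---|---|---|
| 0.3 | 18.79 | 84.2% | 23.31 | 66.6% |
| 0.4 | 18.06 | 87.0% | 21.58 | 73.3% |
| 0.5 | 17.06 | 90.4% | 19.70 | 80.7% |
| 0.6 | 15.76 | 94.2% | 17.62 | 88.5% |

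The change-score test crosses 80% at r of about 0.49. It equals the raw-score test at r = 0.5 and beats it above that. ANCOVA is ahead of both at every r shown. The small degree-of-freedom cost of the covariate is ignored, and nothing is credited to age.

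**3. What the Mann-Whitney test targets.** Illustrative simulations used a five-level 0–100 score, 62 per group and 4,000 runs. The distributions are assumptions.

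| True mean difference | P(higher) + ½P(tie) | Medians | Mann-Whitney rejects | t test rejects |
|---|---|---|---|---|
| 10.25 | 0.619 | 75 v 75 | 68% | 73% |
| 11.0 | 0.568 | 75 v 75 | 29% | 60% |
| 10.5 | 0.532 | 75 v 75 | 10% | 52% |
| −0.5 | 0.428 | 75 v 75 | 32% | 5.7% |

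Several of these distributions have SDs well above 19.7, so the rejection rates should not be set against the planned 80%. The comparison between columns is what matters. Nearly the same mean difference produces very different Mann-Whitney results, and a mean difference near zero with different shapes produces rejection in about a third of runs.

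**4. Age.** This needs no arithmetic. The section promises control for age, and the only tests it names for the primary outcome have no place for a covariate.

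**The case against.** The strongest reply is that little here is an error. Under randomisation an unadjusted t test is valid and, at the back-solved SD, has the planned power. Raw-score, change-score and ANCOVA analyses all target the same expected between-group difference, so preferring ANCOVA is a matter of efficiency. The article does not say that the t test itself adjusts for age; a supplementary model could do that. The statistician for the primary outcome is blinded to allocation, which limits opportunistic choice of test. Satisfaction was lower in these three domains than in the others in the audit, so a ceiling is not assured.

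Much of this stands, and it rules out four stronger readings that a reader might infer.
- *The plan disregards baseline.* The Abstract and Table 1 point the other way, and a t test on change scores would use baseline. What is supported is that the Statistical analysis section makes no provision for it and does not match those two places.
- *The result would be biased.* Randomisation protects the t test.
- *The sample size is too small.* The raw-score test meets 80%. The change-score shortfall depends on a correlation that the article does not give. The analysed number could also exceed 63 per arm, because missing end-of-study scores are replaced by the latest available ones.
- *No mean difference would be reported.* Naming a rank test does not prevent group means from being shown. The supported point is that the primary test would not be a test of that mean difference.

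The reply does not remove the age problem, since no method capable of adjustment is named. Nor does blinding cure the switch: the quantity tested still depends on the shape of the observed data.

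**Conclusion.** The point holds as a specification problem with a modest cost in precision. Two parts follow from the text alone: neither named test can control for age, and the sections disagree on whether an end score or a change is analysed. The Mann-Whitney part holds only if that branch is triggered.

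The size of the precision loss is conditional on the assumed SD and correlations. Against 81% for the raw score, ANCOVA would add roughly 3 to 13 percentage points of power for r between 0.3 and 0.6. Taking Table 1 literally as a change score could cost about 14 points at r = 0.3 or gain about 8 at r = 0.6. The change should be made, but the trial's validity does not hang on it.

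**What to change.** Replace the t-test/Mann-Whitney sentence with one prespecified linear model of the 12-month combined three-domain score on arm, baseline combined score and age. Report the adjusted mean difference in points with a 95% confidence interval, using robust or bootstrap standard errors, whatever a normality check shows. Keep the Mann-Whitney test as a sensitivity analysis only.

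Then align the other places:
- In Table 1, drop the bracketed reference to change, or state that baseline enters as a covariate.
- In the Abstract, say that baseline is a covariate and that the 12-month score is the primary endpoint, and state what role the 3-, 6- and 9-month questionnaires have.
- In Statistical analysis, say that control for age is through the model, and define the age sensitivity analysis relative to it.

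The cost is wording only. Baseline VSQ-9 and age are already in the baseline questionnaire, so no extra patients, visits or data are needed. The change should be dated before outcome data are compared by arm.

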### Recruitment and consent

Prior to each clinic where recruitment is taking place, a member of the clinical team will screen the day’s clinic list to identify eligible patients on the basis of time since transplant and age (inclusion criteria 1 and 2). Patients who meet these criteria will have the study introduced to them at the end of their routine outpatient appointment and their further eligibility assessed against inclusion criteria 3 to 7. The consultant will give eligible patients a Participant Information Sheet and those interested in study participation will have the opportunity to discuss the study with a member of the University of Birmingham research team. The research team will take written informed consent during the clinic from patients who wish to participate and the latter will complete a baseline questionnaire prior to randomisation. Patients who require more time to consider participation will be able to take the study information away and will be contacted by telephone within 7 days by a member of the research team. If a patient agrees to take part over the telephone, a consent form and baseline questionnaire will be posted to them along with a reply-paid envelope for return of the completed documents to the University of Birmingham. Once recruited, participants will stay in the study for 12 months. This will equate to between two and four follow-up appointments since the participants’ usual appointment schedule and frequency will continue to be defined by clinical need regardless of group allocation.

If a patient does not wish to participate in the study, their reason for refusal will be recorded, along with routinely collected information (age, sex and clinic attended). To further understand reasons for participants not taking part, a selection of non-participating patients (*n* = 4) will be invited to take part in a short semi-structured interview (see qualitative study section).

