#### Follow-up

Patients will complete patient satisfaction and summary cost questionnaires after each myVideoClinic or standard hospital appointment. For participants on a 3-monthly follow-up schedule, data will be collected at baseline and at 3, 6, 9 and 12 months. For participants on a 6-monthly follow-up schedule, data will be collected at baseline and at 6 and 12 months. For all participants, the 6- and 12-month questionnaires will collect full data on satisfaction, costs (e.g. health service use, travel and personal expenses), IT issues and HRQoL. Patients who also have appointments at 3 and 9 months after baseline will complete shorter questionnaires at these time points, covering satisfaction and costs only. Questionnaires will be sent to patients in both study arms electronically through the myhealth@QEHB system no more than 7 days after each appointment.

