### Sample size and study power

The sample size for the study has been determined by the effect size needed to detect a clinically significant (10 point) difference between intervention and control groups in the primary outcome measure (patient satisfaction as measured on three domains of the VSQ-9). Assuming a normal distribution of satisfaction scores, a sample size of 62 patients per group would be sufficient to detect a 10-point difference in VSQ-9 scores between groups at 80% power and an alpha of 0.05. Over a 12 month period, an estimated 267 eligible patients will be available for recruitment to the study from the four liver clinics of interest. Annually, approximately 1% of liver transplant patients at UHB undergo a re-transplant and 2% die. Thus, around 21 patients per month will be eligible for recruitment. Audit data collected from one liver clinic in early 2017 suggest that approximately 60% of eligible patients will be willing to participate in the study (13 per month). A previous randomised controlled study of video clinics in diabetes care reported an attrition rate of 30% [12]. Applying this attrition rate to our patient sample, and allowing for participant withdrawals, missing data and losses to follow-up, the required sample size for the study is 90 per group (*n* = 180 total). Recruiting at a rate of 13 patients per month, we anticipate recruitment to take approximately 14 months in total (Fig. 3).

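### The carry-forward rule for missing 12-month VSQ-9 scores lets the pre-randomisation baseline stand in as an outcome, which is expected to dilute the primary treatment effect

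*Protocol article*

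**What the plan says.** All places are in the protocol article.

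- **Missing-data rule (Statistical analysis):** "For patients with missing end-of-study VSQ-9 data, their most recently collected data will be used in the analysis". The main analysis is by intention to treat. It uses an independent t test, or a Mann–Whitney U test if the scores are not normal.
- **When VSQ-9 is measured (Primary outcome measure):** "VSQ-9 data will be collected at baseline and after every video clinic or face-to-face appointment via patient questionnaires".
- **Baseline (Recruitment and consent):** consenting patients "complete a baseline questionnaire prior to randomisation".
- **Six-monthly patients (Follow-up):** "For participants on a 6-monthly follow-up schedule, data will be collected at baseline and at 6 and 12 months". They therefore have one score between baseline and the endpoint.
- **Target difference (Primary outcome measure):** a 10-point difference between arms "at study end (12 months) will be taken as clinically significant".
- **Sample size (Sample size and study power):** 62 per group for 80% power at alpha 0.05, raised to 90 per group using a 30% attrition rate taken from an earlier video-clinic trial in diabetes.

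The only other analyses named for the primary outcome are a per-protocol analysis, an age sensitivity analysis and a subgroup analysis by engagement. None of them addresses missing scores.

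**The concern.** The rule is last observation carried forward, and baseline is one of the observations that it can carry. A patient who returns no follow-up questionnaire has the baseline score as the latest value, and an intention-to-treat analysis gives no reason to leave that patient out. For a six-monthly patient, two missing questionnaires (6 and 12 months) are enough.

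Baseline precedes randomisation, so its expected difference between arms is zero. Each such patient enters the 12-month comparison as if the intervention had done nothing. At stake is the primary estimate, which is judged against a fixed 10-point criterion: the rule can move its expected value below 10 even when the true effect is exactly 10.

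**Working it through.** **1. The plan's own figures.** No SD is stated. With two-sided alpha 0.05 (sidedness is not stated, so this is assumed), 80% power and a 10-point difference, 62 per group implies

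SD = 10 × √(62/2) / (1.960 + 0.842) = 19.9.

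An SD of 20 gives 63 per group. This shows that 62 is consistent with an SD of about 20; it is not an independent reproduction. For attrition, 62/0.70 = 88.6, so 89, against 90 stated; 63/0.70 = 90 exactly. The figures hang together.

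**2. Expected difference under the rule.** Let δ be the true difference, c the change over time common to both arms, and f1 and f0 the shares of the intervention and control arms with only a baseline score. Assume a constant effect over follow-up and missingness unrelated to the scores.

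- Intervention mean minus baseline mean: (1 − f1)(c + δ)
- Control mean minus baseline mean: (1 − f0)c
- Difference: (1 − f1)δ + (f0 − f1)c

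With f1 = f0 = f this is δ(1 − f), whatever c is. With c = 0 it is δ(1 − f1).

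**3. Size, equal shares, δ = 10, 90 per arm, SD 19.9 (variance 395).** Mixing treated and untreated values adds 100·f(1 − f) to the intervention-arm variance (taking c = 0), so SE = √[(2 × 395 + 100·f(1 − f))/90]. At f = 10%, SE = √(799/90) = 2.98 and power = Φ(9.0/2.98 − 1.96) = 85.6%. The like-for-like comparator is the same t test with baseline barred, so that 90(1 − f) per arm contribute a post-randomisation score.

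| f | Rule as written: difference | Power | Baseline barred: difference | Power |
|---|---|---|---|---|
| 0% | 10.0 | 92.2% | 10.0 | 92.2% |
| 10% | 9.0 | 85.6% | 10.0 | 89.3% |
| 15% | 8.5 | 81.2% | 10.0 | 87.5% |
| 20% | 8.0 | 76.2% | 10.0 | 85.5% |
| 30% | 7.0 | 64.5% | 10.0 | 80.6% |

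Simulation of the rule (4,000 trials per row, SD 19.8, assumed correlation 0.5 between visits, 30% missing at 12 months) agrees: 9.0 points and 85% at f = 10%, 8.5 and 81% at 15%, 7.0 and 64% at 30%.

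**4. Unequal shares with a common trend.**

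- f1 = 30%, f0 = 10%, c = +5: 7.0 − 1.0 = 6 points.
- f1 = 10%, f0 = 30%, c = +5: 9.0 + 1.0 = 10 points.
- f1 = 10%, f0 = 40%, c = +10: 9.0 + 3.0 = 12 points.
- No true effect, f1 = 5%, f0 = 25%, c = +10: 0 + 2.0 = a spurious 2 points. In simulation the type I error is then about 10 to 11%.

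**5. Other analyses as benchmarks.** If all 30% without a 12-month score are dropped, 63 per arm remain: SE = 19.9 × √(2/63) = 3.54, and an unadjusted t test has 80.6% power. Adjusting those same patients for baseline at correlation 0.5 multiplies the variance by 1 − 0.25 = 0.75: SE = 3.07, power about 90%. The rise from about 80% to about 90% is due to covariate adjustment, not to removing carry-forward.

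**The case against.** The strongest reply is that the size is unknown and may be small. Patients have two to four follow-up appointments, each with a VSQ-9, and paper questionnaires go to those with technical problems. The 30% is borrowed from another trial and covers withdrawal, missing data and loss to follow-up together; it does not forecast patients with no follow-up score. All of this stands. A reader might infer that the full 30% would carry baseline and that the effect will come out at 7 points. The article does not support that: 7 points is the end of the range, and it needs every missing patient to have no follow-up score.

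A second reply is that carry-forward costs little power. This stands in part. Against an unadjusted complete-case t test (about 80%), the rule as written has more power until about half of the missing patients are baseline-only (f = 15%, 81%). With equal shares and no time trend its type I error stays near 5%. So setting the rule against a 90% baseline-adjusted analysis would overstate its cost. But power is not the main harm. The expected estimate falls below 10 for every f above zero with equal shares, and barring baseline gives more power with the same test.

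A reader might also see a contradiction with the Abstract, which says that "The primary outcome will be analysed using baseline and 3-, 6-, 9- and 12-month questionnaires", while a t test takes one value per patient. The same Abstract sentence ties this to each patient's appointment frequency, tests could be run at each time point, and the carry-forward rule itself draws on earlier questionnaires. This is a secondary matter and the point does not depend on it.

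Finally, a fuller analysis plan may narrow the rule. It may, but the published sentence states the rule without that limit, so the plan would have to change it and not merely add detail.

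**Conclusion.** The point holds as a defect in a stated rule, of conditional size. As written, the rule admits a pre-randomisation score as a 12-month outcome, and with equal baseline-only shares a true 10-point difference is then estimated as 10 × (1 − f). Across the range that the article allows, this is from 10 points (f = 0, no harm if the effect is constant) down to 7.0 points (f = 30%), with power from about 92% down to about 64%. These figures rest on a back-solved SD of about 20, a two-sided test, 90 per arm, a constant effect, equal shares and missingness unrelated to the scores.

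It would go too far to say that the effect is certain to be pulled towards zero. That is the expected direction when the baseline-only shares are similar in the two arms or there is no common change over time. With unequal shares and a common trend the bias can go either way. Patients know their allocation, so unequal response is plausible, but the article gives no figure for it.

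**What to change.** State that a baseline VSQ-9 score is never used as an outcome value.

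- **Minimum:** limit any carried value to scores collected after randomisation. This takes a few words and removes the dilution worked out above. Patients with no follow-up score then contribute no outcome, and their number should be reported by arm.
- **Preferred:** replace the rule with a repeated-measures model on all post-randomisation VSQ-9 scores, adjusted for baseline score and age, with the 12-month contrast as the primary estimate. The article already intends to control for age, which neither of its two tests does. Add one missing-not-at-random sensitivity analysis, for example shifting the missing intervention scores downwards by stated amounts.

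The cost is about one paragraph of text and slightly more programming, with no new data. The drawback of the model is that 3- and 9-month scores are absent by schedule for six-monthly patients, so it must treat these as visits not planned and not as missing. Any comparison of power between options should be like for like, with the same adjustment on both sides. The change should be made before the analysis.
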